## Study groups

The target population for this study is patients who underwent preoperative assessment for elective surgery at Barnes Jewish Hospital in St. Louis, Missouri between 16 January 2014 and 7 October 2015. Over 70% of patients undergoing elective surgery are assessed by the centre for preoperative assessment and planning (CPAP) clinic before surgery. Reasons for no assessment include urgent surgery, geographical limitations or surgeon preference. Inclusion criteria include age 18 or older, ability to read the English consent form, ability to consent and plans to undergo elective surgery. During the analysis phase, patients are excluded from participation in SATISFY-SOS if they have undergone surgery within 60 days of their planned surgery date.

Approximately 65% of all eligible patients consent to participate in the study. Reasons for non-participation include patient refusal (∼70% of cases), lack of nurse time or training (∼20%), or lack of English literacy (∼10%). A study comparing participants to non-participants showed no major differences in characteristics.^19^ Approximately 92% of all consented patients complete a baseline survey. Reasons for lack of complete participation include insufficient time or changing their mind. Overall, the estimated number of eligible patients per YEAR is 15 500, the estimated number of consenting patients per year is 10 000, and the estimated number of baseline survey records per year is 9200. Approximately 16 000 baseline survey records are available in the time period specified for this study (16 January 2014 to 7 October 2015).

For the purposes of this substudy, only the first complete record for each patient (ie, baseline survey and corresponding 30-day survey) will be included in the final data set (∼94% of the available records). This practice ensures that each record is statistically independent from all the other records.

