## Statistical considerations

### Sample size calculations

The required sample size is calculated based on the primary outcome, which is a fall within 30 days of surgery. Appropriate logistic regression models contain at least 10 ‘events’ per predictor variable.^20^ Since our prespecified model for postoperative falls includes 13 dependent variables (see the Analysis section), a sample with at least 130 events is required. In our population, preliminary work shows that ∼10% of patients report falling in the month following surgery. Thus, the minimum sample size needed for this study is 1300 patients.

Currently, our database contains over 9000 complete records (ie, baseline and 30-day survey) after the 16 January 2014 start date. To meet statistical assumptions of independent observations, we estimate that ∼600 records from patients with at least one previous entry in the data set will be excluded. We estimate that an additional 600 records will be excluded due to inappropriate time intervals (baseline survey to surgery <0 or >59 days; surgery to 30-day survey <20 or >120 days; or surgery to 1-year survey <275 or >455 days). Thus, our final sample size will be ∼7800.

Within this final sample, two versions of the 30-day (V.2 and V.3) and 1-year surveys (V.1 and V.2) were administered. Only V.3 of the 30-day survey and V.2 of the 1-year survey contain a validated falls question, as recommended by the Prevention of Falls Network Europe consensus group.^21^ The difference in question phrasing caused statistically significant differences in the percentage of patients reporting postoperative falls (5.5% vs 10% at 30 days and 18% vs 28% at 1-year, p<0.001). Out of the available records, about 20% (1500) completed V.3 of the 30-day survey, which is more than the 1300 required for the primary outcome. Thus, to maximise outcome validity, only these versions will be used for postoperative falls. In contrast, the readmission question contained only minor differences (‘Were you readmitted to the hospital?’ for V.2 vs ‘Check all that apply […] admitted to a hospital’ for V.3). The percentage reporting readmission was similar between surveys (5.2% vs 5.7%, p=0.416), so the results from both versions will be combined. The remaining outcomes were identical and will use all available data from both versions of the 30-day and 1-year surveys.

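### Keeping each patient's first complete record before restricting falls to the validated survey version discards usable primary-outcome records

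*Protocol article*

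**What the plan says.** Study groups sets the record rule: "only the first complete record for each patient (ie, baseline survey and corresponding 30-day survey) will be included in the final data set". Its purpose is given in the next sentence: "This practice ensures that each record is statistically independent from all the other records". A complete record is defined there by having both surveys, without regard to version.

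Sample size calculations applies the rule. It starts from the statement that "our database contains over 9000 complete records (ie, baseline and 30-day survey) after the 16 January 2014 start date", estimates that about "600 records from patients with at least one previous entry in the data set will be excluded", adds that "an additional 600 records will be excluded due to inappropriate time intervals", and concludes: "Thus, our final sample size will be ∼7800". The split between survey versions is then described as a feature of that final sample. Because the two wordings of the falls question gave different fall percentages, the section decides: "Thus, to maximise outcome validity, only these versions will be used for postoperative falls". About 20% of the records, put at 1500, have V.3 of the 30-day survey.

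The article makes no provision for choosing a patient's first V.3 record for the falls models.

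**The concern.** Read in sequence, the two rules lose data that neither rule needs to lose. De-duplication ignores survey version, and the version restriction then works on what is left. A patient whose first complete record in the window is V.2 and whose second is V.3 has the second removed as a repeat and the first set aside for falls. That patient contributes nothing to the primary outcome. The same can happen at 1 year with V.1 and V.2.

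The loss falls on the smallest analysis in the plan. The other outcomes draw on about 7800 records, the primary outcome on about 1500. The protocol concedes that its detectable effect for falls is larger than its 20% minimum important difference, and, under Limitations, that there may be too few outcomes to test every interaction of interest. The analysis also tests at α=0.01, whereas the power statement uses α=0.05.

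**Working it through.** **Inputs from the protocol.** More than 9000 complete records; about 600 repeats removed; about 600 removed for time intervals; V.3 about 20% (1500); 30-day fall proportion about 10%; 26% with preoperative falls; 13 model variables at 10 events each; 80% power, two-sided α=0.05 for planning and 0.01 for analysis; window 16 January 2014 to 7 October 2015 (about 20.7 months).

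**1. The protocol's counts reproduce.**
- Minimum sample: 13 × 10 / 0.10 = 1300.
- Final sample: 9000 − 600 − 600 = 7800.
- V.3 share: 1500/7800 = 19.2%, against 1500/9000 = 16.7%. The stated 20% fits the de-duplicated sample better, so the 1500 appears to be net of the loss.
- Expected events: 1500 × 0.10 = 150, or 150/13 = 11.5 per variable, against 130 required.

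**2. The protocol's detectable effect reproduces.** Take 10% as the overall fall proportion and RR as the ratio of fall proportions. Then p0 = 0.10/(0.74 + 0.26·RR) and p1 = RR·p0. With n0 = 0.74N and n1 = 0.26N,

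power = Φ{[(p1 − p0) − z(1−α/2)·√(0.10·0.90·(1/n0 + 1/n1))] / √(p0(1−p0)/n0 + p1(1−p1)/n1)}.

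At RR = 1.58, p0 = 8.69% and p1 = 13.73%. With N = 1500 the power is 79.2%, and 80% power needs N = 1531, within about 2% of 1500. Solved for RR at N = 1500, the detectable increase is 58.7%, against the stated 58%.

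**3. How many patients could be recovered (assumptions).** The protocol gives neither the V.2-to-V.3 changeover date nor the number of patients with a V.2 record followed by a V.3 record. Three illustrative cases, each treating the 600 repeats as 600 patients with two records:
- Single changeover after 80% of the window, fixed 2-month gap between operations, first operation uniform over the remaining time: 600 × 2/(20.7 − 2) ≈ 64. A 3-month gap gives 600 × 3/(20.7 − 3) ≈ 102.
- Version unrelated to record order: 600 × 0.8 × 0.2 = 96.
- V.3 as the last fifth of the period, both records uniform in time: 600 × 2 × 0.8 × 0.2 = 192.

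The ceiling is about 600, if every repeat qualified. Records that fail the interval rules would reduce all of these.

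**4. Effect on the primary analysis** (formula of step 2, 80% power for the detectable increases):

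| Recovered | N | Events | Events per variable | Detectable increase, α=0.05 | Detectable increase, α=0.01 | Power for RR 1.58, α=0.05 / 0.01 |
|---|---|---|---|---|---|---|
| 0 (plan) | 1500 | 150 | 11.5 | 58.7% | 74.0% | 79.2% / 60.0% |
| 64 | 1564 | 156 | 12.0 | 57.3% | 72.2% | 80.8% / 62.1% |
| 96 | 1596 | 160 | 12.3 | 56.6% | 71.3% | 81.5% / 63.1% |
| 192 | 1692 | 169 | 13.0 | 54.7% | 68.8% | 83.6% / 66.1% |
| 600 (ceiling) | 2100 | 210 | 16.2 | 48.2% | 60.5% | 90.2% / 76.7% |

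**The case against.** The strongest defence is that nothing here is misstated. The rule, its reason and its cost (about 94% of records kept) are disclosed, and the sample size rests on a count that already appears to absorb the loss. That stands: this is a point about efficiency, not an error in a figure.

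The second defence is substantive. The exposure is falls in the 6 months before surgery, while the exclusion for recent surgery reaches back only 60 days. A recovered later record may therefore count, as preoperative falls, events that followed the patient's earlier operation. Taking the first record limits that overlap and keeps one cohort and one baseline for all outcomes. A reader might infer that the present rule serves no purpose; that is not so. The advantage is only partial, though. The first complete record in the window is not necessarily the patient's first operation, so the same overlap can already occur, and a sensitivity analysis can show whether it matters.

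Third, the gain is small and its size is assumed. That also stands. Even at the ceiling of 600 the detectable increase is about 48%, still far above 20%.

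Three stronger readings are tempting and lack support:
- That the primary analysis is short of events. About 150 are expected against 130 required, and the protocol's concession concerns interaction terms only.
- That the authors dismissed the loss as a small share of all records. The protocol reports the share retained and makes no argument about the V.3 subset.
- That the falls sample is materially biased. Patients with an earlier V.2 record are left out of it, but nothing in the document gives the size or direction of any bias.

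**Conclusion.** The point holds as a minor, avoidable loss of collected primary-outcome data. The two rules do act in sequence, and the stated reason for the first is fully met by one record per patient within each analysis. The stated figures are sound on the protocol's own criteria and do not need correcting.

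Under the timing assumptions shown, roughly 60 to 190 patients (about 4% to 13% of 1500) and about 6 to 19 events would be regained. The detectable increase would move from about 59% to 55–57% at α=0.05, and from about 74% to 69–72% at α=0.01. These are illustrations, not bounds. The bounds are none and about 600, and only a count from the database can settle the number. The same reasoning applies to 1-year falls, for which the document gives no figures to size the loss.

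**What to change.** Apply the one-record rule per outcome. For the falls outcomes, restrict to the validated version first (V.3 at 30 days, V.2 at 1 year), apply the interval rules, and then keep each patient's first eligible record. Keep the first complete record for all other outcomes. Report how many patients the change adds, and give the falls results under the protocol's present first-record rule as a sensitivity analysis.

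The cost is one sentence and a changed de-duplication step. Analysis is to begin only after the protocol is accepted, so the change can still be prespecified. There are two downsides to state. A small number of patients will contribute different records to different models. Some recovered records may also have a 6-month preoperative fall window that overlaps recovery from an earlier operation, which the sensitivity analysis is there to examine.

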## Recruitment

Nurses at the CPAP clinic assess patient eligibility, recruit patients to participate, and obtain written consent using the consent form found in the online supplementary material. This consent form serves as the source of patient information for the study. While most patients decide whether or not to participate at this time, a patient can decide to participate any time between his or her CPAP visit and his or her surgery day. For patients who need special assistance, such as those who are blind or cannot physically sign a form, a witness can be obtained. However, in practice, this rarely occurs. No arrangements are made for non-English speakers, mentally ill, children, or those suffering from dementia since those are excluded groups (see the Study groups section). Patients receive no compensation for participation. If patients agree to participate, the CPAP nurse asks them to complete a brief baseline survey at the time of consent. Approximately 30 days and 1 year following surgery, they receive similar follow-up surveys. Both surveys were designed to take 10–15 min to complete. The SATISFY-SOS research team holds monthly update meetings with all CPAP nurses to inform them about study progress and to encourage optimal recruitment.

10.1136/bmjopen-2016-011570.supp3Supplementary data

## Data

### Data to be collected

Incomplete follow-up is a major source of bias in many long-term observational cohort studies. To maximise completeness of 30-day and 1-year follow-up data, the following sequence of contact methods is performed. First, the survey is emailed up to three times starting ∼20 days after the surgery date. For those who did not provide an email or who do not respond to the emails, a paper survey is also mailed 25 days after the surgery date. If a patient does not respond to the first paper survey, a second paper survey is mailed 21 days later. If the second paper survey is not returned, the patient is phoned up to five times. Using this aggressive protocol, the 30-day survey response rate between 16 January 2014 and 7 May 2015 was ∼55%. An identical process occurs for the 1-year survey, beginning 365 days after the surgery date. For the date ranges included in this study, two versions of the 30-day survey (V.2 and V.3) and two versions of the 1-year survey (V.1 and V.2) were administered to participants. See online supplementary material to view these surveys.

10.1136/bmjopen-2016-011570.supp4Supplementary data

10.1136/bmjopen-2016-011570.supp5Supplementary data

10.1136/bmjopen-2016-011570.supp6Supplementary data

10.1136/bmjopen-2016-011570.supp7Supplementary data

Access to the SATISFY-SOS data is limited to investigators and staff who: have access to the Department of Anesthesiology desktop computers, have a computer account with the Department of Anesthesiology, use an IP address from within the department offices, have written permission to analyse the data from the principal investigator, and have authorised access to the database. For this project, the investigators formulated a list of requested data. They will provide that list to the informaticist, who manages the SATISFY-SOS database and has access to other medical records data. Using queries in MetaVision (iMDsoft, Needham, Massachusetts, USA), the informaticist will provide the requested survey and medical record data to the investigators. The query start date will be 16 January 2014 since important survey revisions occurred before this date.

Table 1 contains all variables to be collected for the study, along with the form of the variable, its source, time point for collection and whether or not it comes from a standardised tool. Of note, the informaticist performs rigorous data validation on each queried variable. If continuous variables are found to exhibit non-linearity, they will be categorised in accordance with their distribution.

**Table 1 BMJOPEN2016011570TB1:** Characteristics of all variables used in this study

Type	Variable name	Form	Source	Time	Use of standardised tool
Explanatory	Preoperative falls	0, 1, 2, 3+	Survey	BL	Yes^21^
	Charlson Comorbidity Index	Ordinal, 0–12	CPAP H&P	BL	Yes^29^
	ASA physical status	Ordinal, 1–6	Anaesthesia record	Surgery	Yes^30^
	Procedural cardiac risk	Ordinal, 5 categories from high to low	CPAP clinician	BL	Yes^31^
Outcome	Postoperative falls	Binary (V.2); 0, 1, 2, 3+ (V.3)	Survey	30 days, 1 year	Yes^21^
	Functional dependence	Ordinal, 0–100 by 5	Survey	30 days, 1 year	Yes^32^
	Physical quality of life	Continuous, 0–100	Survey	30 days, 1 year	Yes^33^ ^34^
	Mental quality of life	Continuous, 0–100	Survey	30 days, 1 year	Yes^33^ ^34^
	In-hospital complications	Dichotomous	Survey	30 days	No
	Readmission	Dichotomous	Survey	30 days	No
Demographic	Age	Continuous	Medical record	BL	NA
	Sex	Dichotomous	Medical record	BL	NA
	Race	Nominal	Medical record (patient report)	BL	NA
	Ethnicity	Hispanic/Latino or not	Medical record (patient report)	BL	NA
	Body mass index	Continuous	CPAP nurse	BL	Yes
Confounder	Functional dependence	Ordinal, 0–100 by 5	CPAP nurse	BL	Yes^32^
	Physical quality of life	Continuous, 0–100	Survey	BL	Yes^33^ ^34^
	Mental quality of life	Continuous, 0–100	Survey	BL	Yes^33^ ^34^
	Smoking status	Current, past, never	CPAP physician or nurse	BL	NA
	Physical activity level	<4, 4–6, 6–10, >10 (METs)	CPAP physician	BL	Yes^35^
	Incontinence	Dichotomous (any issue)	CPAP nurse	BL	Yes^32^
	Toileting difficulty	Dichotomous (any issue)	CPAP nurse	BL	Yes^32^
	Mobility issue	Dichotomous (any issue)	CPAP nurse	BL	Yes^32^
	Neurological impairment (stroke, paraplegia or quadriplegia, Parkinson disease or multiple sclerosis)	Dichotomous	CPAP H&P	BL	No
	Chronic pain	Dichotomous	CPAP physician ROS	BL	No
	Dizziness/vertigo	Dichotomous	CPAP physician ROS	BL	No
	Depression	Dichotomous	CPAP H&P	BL	No
	Anxiety	Dichotomous	CPAP H&P	BL	No
Descriptive	Fall-related injury	Check all that apply	Survey	BL, 30 days, 1 year	No
	Days from BL to 30 days survey	Continuous	BL survey, Press Ganey	BL completion date to 30 days process date	NA
	Days from BL to 1 year survey	Continuous	BL survey, Press Ganey	BL completion date to 1 year process date	NA
	Surgery type	10 categories	Medical record	BL	NA
	In-hospital falls	Dichotomous	Survey (V.3 only)	30 days	Yes^21^
	In-hospital heart problem or stroke	Dichotomous	Survey	30 days	No
	In-hospital lung complication	Dichotomous	Survey	30 days	No
	In-hospital blood clot	Dichotomous	Survey	30 days	No
	In-hospital kidney or intestine complication	Dichotomous	Survey	30 days	No
	In-hospital nerve injury	Dichotomous	Survey	30 days	No
	In-hospital infection	Dichotomous	Survey	30 days	No
	In-hospital delirium	Dichotomous	Survey	30 days	No
	Other in-hospital complication	Dichotomous	Survey	30 days	No

ASA, American Society of Anesthesiology; BL, baseline; CPAP, centre for preoperative assessment and planning; H&P, history and physical; METs, metabolic equivalents; NA, not applicable; ROS, review of systems.

### Data handling and record keeping

All supplementary electronic data are collected from existing clinical records including MetaVision; CIDER; Compass; Allscripts TouchWorks; National Surgery Quality Improvement Program (NSQIP); and ClinDesk. SATISFY-SOS databases are hosted on a firewall-secured network server managed by the Department of Anesthesiology. The server is securely housed behind two locked doors within the departmental office suite and maintained and managed by the departmental IT team. The IT team patches and upgrades the server operating system on a routine basis and will employ virus protection and encryption to ensure proper data security. Incremental backups start daily; full backups start weekly. Only the project informaticist, data manager and director(s) have full access to these databases, which are also password-protected and encrypted for additional protection. Investigators have ‘read-only’ access to these databases for quality assessment and improvement.

Hard copies of the baseline surveys are collected daily from the CPAP clinic and securely stored behind two locked doors within the Department of Anesthesiology. Baseline completed paper surveys are scanned into a digital image format (compressed TIFF). The digital image files are indexed and stored on a research file server that is attached to a private network with no public access. Only Health Insurance Portability Accountability Act (HIPAA)-trained employees of the Department of Anesthesia or Barnes Jewish Healthcare are granted access to resources on this network. Access to the file server itself is further restricted to SATISFY-SOS team members.

Baseline surveys are processed by Solutions Data Systems. The digital image files are transmitted to Solutions Data Systems via secure file transfer protocol, which employs the same encryption method as secure web sites (128-bit or better Secure Sockets Layer (SSL)). Solutions Data Systems performs data entry of the digital image files, and prepares a monthly report of the data. That report is transmitted back to the research team via the same secure file transfer protocol connection. When data entry has been confirmed, Solutions Data Systems deletes the digital image file from its servers.

Press Ganey, a vendor specialising in patient survey distribution and collection disseminates, collects and processes 30-day and 1-year surveys. Its dedicated quality improvement team monitors and fine-tunes its quality assurance methods. For example, paper surveys processed through automated scanning are all manually checked, and a manager listens to 10% of telephone surveys.

Survey email, mail and call lists are generated at Washington University in a similar manner to mailing lists for billing services. For each patient and date of service, a unique ID is generated and never duplicated. This unique ID is a nonsensical number only meaningful to the research team. Initial survey collection attempts occur via email. The email letter contains a secure link to an encrypted electronic survey environment. This individual survey link can only be accessed once by the patient.

Patients without email addresses, or patients who did not respond to the email, are contacted by postal mail and then by telephone. On a weekly basis, packets specifically addressed to patients are generated. The packet includes a cover letter with the patient's name, mailing address and unique ID included. The cover letter is the only document with information linking the patient to a unique ID. The packet also includes a paper copy of the survey with only the patient's unique ID already printed on all pages as well as a stamped, self-addressed return envelope for return of the completed survey via the postal service. The survey pages will not include any protected health information. The survey responses are returned to a PO Box designated for this project.

Press Ganey picks up the surveys from the PO Box and converts them from a paper format to an electronic format with discrete variables, including the unique ID for each survey. Press Ganey makes image and data files available for File Transfer Protocol retrievals by the study team on a daily basis. For phone calls, Press Ganey uses an internal phone survey centre. All telephone surveys are recorded and available for future quality checks for performance improvement. These recordings are made available to the research team. The research team, at any time, may monitor real-time patient interviews for additional quality assurance purposes.

Press Ganey stores the survey hard copies for 90 days while the study team conducts spot check quality assessments of the scanned data. The company then shreds the paper copies. Similarly, Press Ganey will hold copies of the electronic files and electronic recordings for 90 days, after which the electronic files are removed permanently from its system (and then only maintained by Washington University). During this 90-day period, the study team conducts additional quality assessments of the converted data.

